### Participants

Individuals diagnosed with NSCLC stages I–III who have completed their primary cancer treatments within 12 months and have obtained a medical clearance (from a general practitioner or medical team) to engage in RT will be recruited. Participants will be excluded if they (1) have a diagnosis of advanced (stage IV) lung cancer or diagnosis of small cell lung cancer; (2) are not comfortable having study staff visit their homes for RT sessions; (3) have any neuromuscular, cardiovascular, or psychological condition (assessed using self-report questions during eligibility screening) precluding safe exercise; (4) have participated in structured RT ≥ 2 times/week for the past 6 months; or (5) are unable to read/understand English. Further description of eligibility criteria is provided in Table 1.

**Table 1 Tab1:** Eligibility criteria

**Inclusion criteria**	• Completed definitive treatment for localized NSCLC (stages I–III) within 12 months of completion • Has access to stable Internet access for Zoom participation • Willing to complete an 8-week, home-based intervention program that includes face-to-face and Zoom interaction • Willing to consider behavior change at this time • Able to speak and read English • Capable of informed consent • Has obtained medical clearance from a medical practitioner or medical team
**Exclusion criteria**	• Individuals with a known diagnosis of advanced lung cancer (stage IV; due to potential added burden) or diagnosis of small-cell lung cancer • Anyone for whom physical activity is not recommended • Are not comfortable having study staff visit their homes for exercise sessions • Have any neuromuscular, cardiovascular, or psychological condition precluding safe exercise • Have participated in structured RT ≥2 times/week for the past 6 months • Are unable to read/understand English

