Within a week of the first anticipated invitation arrival, telephone contact will be initiated with the recipients by a member of the research team. Over the phone, using a script, the research specialist will screen individuals indicating interest in participating to determine eligibility. Additional follow-up telephone contact will be made after the individual has had adequate time (~1 week) to make a decision and speak with a family member about participating. These telephone interactions are designed to strengthen trust in the research team, build credibility, and increase understanding of the study. During this call, interested individuals will be provided with detailed information about the study purpose/aims, protocol, potential benefits, and risks and be asked to answer further eligibility questions. Individuals who are eligible and remain interested will be asked to provide verification of medical clearance and provide informed consent to participate prior to any study activities.

Pre- and post-intervention data collection will take place at the University’s Department of Exercise Science. Exercise sessions will take place in participants’ homes or other convenient locations. Informed consent will occur prior to baseline testing, where a member of the study team will review the consent form in detail and answer any further questions participants might have. Every effort will be made by study staff to ensure the informed consent is understood in its entirety prior to signing.

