### Intervention

The hybrid RT program will include a combination of in-person and virtual delivery of live exercise sessions (Table 2). The intervention will be delivered by study staff specifically trained in the delivery of exercise programs for individuals with cancer. The first 2 weeks will include a member of the study team visiting the home of participants (or other mutually agreed upon private location) two times per week to deliver supervised exercise sessions. The purpose of this phase is to (1) determine a safe place to exercise in the individual’s home or mutually agreed upon, private location and (2) provide in-person instruction on safe exercise technique and general procedure for exercise sessions (sets, repetitions, clusters, anchoring of perceived exertion/dyspnea scales, etc.). Selection of exercises and loading will be based on each individual’s strength levels, mobility, and any physical limitations. Participants will be provided dumbbells, kettlebells, and suspension training bands (TRX, San Francisco, USA) to complete the home-based exercises. In addition to exercise selection and the delivery of exercise sessions as above, the initial 2 weeks of the study period will also be used to guide participants on how to use the computer tablets, log in for exercise sessions, and record their exercise participation/RDI. Moreover, written instructions in plain language will be provided. Tablet stands will also be provided to allow for more flexibility regarding the placement of tablets for easy viewing.

**Table 2 Tab2:** Overview of hybrid delivery approach for the program

	Weeks																					
	1		2		3			4			5			6			7			8		
Video					X	X	X	X	X		X	X	X	X	X		X	X	X	X	X	
In person	X	X	X	X						X						X						X

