## Discussion

The primary purpose of this trial is to assess the feasibility of a hybrid delivery of cluster set RT for individuals previously treated for NSCLC. Publication of this protocol is to enhance the transparency around trial success, outcomes of interest, and to aid in the replicability of our protocol.

Progress in improving exercise capacity and exercise participation in this complex clinical population is likely to be supported through individualized approaches that are patient-focused. This single-arm study will examine the intervention feasibility in individuals with NSCLC. Novel aspects of this trial include (1) the investigation of a hybrid delivery of exercise prescription, combining supervised, home-based sessions and distant video-conferencing sessions, and (2) the inclusion of a method of exercise prescription specifically aimed at reducing symptom burden in NSCLC. Despite the potential applications and health benefits of this program, a number of unknowns remain. Specifically, the cluster set design may be different conceptually to what individuals may perceive in considering participation in a more “traditional” resistance exercise program. As such, it is unclear if this will be a feasible approach to delivering resistance exercise, particularly using the hybrid model of in-person and virtual sessions. Moreover, individuals may not be comfortable with researchers coming to their home to deliver the intervention. We have attempted to address this by offering the alternative of a mutually agreed-upon, safe location. However, we will track reasons for non-participation with a particular focus on comfortability with home visits with the intention that these results may guide the design of similar interventions in the future.

At the completion of this study, we expect to have gathered critical information on the feasibility of a hybrid delivery of cluster set RT to individuals previously treated for NSCLC. Our assessments of recruitment, retention, fidelity, and acceptability will provide important information on whether progression to a randomized controlled trial is warranted. Further, qualitative exit interviews will provide us with important information regarding elements of the trial that need to be revised in accordance with participant feedback.

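### The exclusion for discomfort with home visits has no exception, although the protocol says another location was offered to address that discomfort

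*Protocol article*

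**What the plan says.** **Eligibility.** Exclusion (2) in the Participants text removes people who "are not comfortable having study staff visit their homes for RT sessions". Table 1 repeats it: "Are not comfortable having study staff visit their homes for exercise sessions". Neither version mentions another place. A separate inclusion line in Table 1 requires people to be "Willing to complete an 8-week, home-based intervention program that includes face-to-face and Zoom interaction".

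**Where sessions take place.** The section on recruitment and screening places exercise sessions in participants' "homes or other convenient locations". The Intervention section describes a staff member in the first 2 weeks "visiting the home of participants (or other mutually agreed upon private location) two times per week to deliver supervised exercise sessions".

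**Why another place is offered.** The Discussion notes that people may be uneasy about researchers coming to their home. It then says: "We have attempted to address this by offering the alternative of a mutually agreed-upon, safe location". It adds that "we will track reasons for non-participation with a particular focus on comfortability with home visits".

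**Recruitment.** Success is 15 people recruited in 1 year (Pre-established criteria for success; Outcome measures). The Limitations section says the pool was kept broad on purpose, because exercise trials in lung cancer have had trouble with accrual.

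**The concern.** Eligibility and delivery give different answers for the same person. Someone who does not want staff at home, but would train at an agreed private place, is the person the Discussion has in mind when it describes the alternative. Under exclusion (2) that person is ineligible.

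Two things are at stake. The first is recruitment: people who could take part are turned away in a trial whose own success criterion is reaching 15 in a year. The second is how the reason is recorded. The trial wants to learn how far home visits deter participation, yet the rule makes such a person a screening exclusion rather than someone who was eligible and declined. A later randomised trial would read those two categories differently.

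**Working it through.** The plan gives no figure to reproduce, so the check sets the sections side by side.

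1. **Scope of the exclusion.** The text and Table 1 both make discomfort with home visits sufficient for exclusion. Willingness to train elsewhere does not change the result.
2. **Scope of delivery.** Both the recruitment section and the Intervention section permit another place. Neither says that its purpose is to accommodate people uneasy about home visits; only the Discussion does.
3. **Does another criterion require home visits?** The Table 1 inclusion line asks for willingness to do a home-based programme with face-to-face and Zoom contact. It does not require staff to enter the home. Table 2 shows 4 in-person sessions in weeks 1–2 and one in each of weeks 4, 6 and 8, so 4 + 3 = 7 in person. Weeks 1–2 have 4 sessions and weeks 3–8 have 6 × 3 = 18, so the total is 22. The other 22 − 7 = 15 are by video. The exclusion therefore concerns the 7 in-person sessions, which the protocol allows elsewhere.
4. **The pilot.** The 2–3 pilot individuals undergo the same screening but exercise in the laboratory. Read literally, the rule would exclude them over a home visit that the pilot does not involve.
5. **Result for one person.** Uncomfortable with home visits, willing at another place: ineligible under Participants and Table 1, accommodated under Intervention and Discussion. Both cannot be followed.

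**What can be said about size.** The documents give no rate of discomfort, so the following rests on assumed values. Let *f* be the fraction of otherwise eligible people who are uncomfortable with home visits. Let *r* be their uptake with the alternative on offer, relative to everyone else's uptake (0 to 1).

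- Uptake among those left after the exclusion, divided by uptake if everyone were kept in the denominator and offered the alternative: 1 / [(1 − *f*) + *f r*].
- Share of possible recruits lost to the exclusion: *f r* / [(1 − *f*) + *f r*].

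| Assumed *f* | Uptake ratio, *r* = 0 | Recruits lost, *r* = 0 | Uptake ratio, *r* = 1 | Recruits lost, *r* = 1 |
|---|---|---|---|---|
| 10% | 1/0.90 = 1.11 | 0 | 1.00 | 10% |
| 20% | 1/0.80 = 1.25 | 0 | 1.00 | 20% |
| 30% | 1/0.70 = 1.43 | 0 | 1.00 | 30% |

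The ratios 1.11 to 1.43 are upper bounds. They hold only if none of these people would enrol, and then the exclusion loses no recruits. If they would enrol as readily as others, the ratio is 1.00 and the whole effect is lost recruits. The two harms cannot both be at their maximum.

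**The case against.** The strongest reply is that this is awkward wording with little consequence. Its parts are:

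- **The alternative still has a use.** It can serve people who accept home visits but lack space or privacy, or find another place more convenient. This stands, and it would be too strong to say that the exclusion makes the alternative inoperative. But it is not the purpose the Discussion gives.
- **Tracking is not defeated.** The Discussion promises to track reasons for non-participation in general, and failing screening over home visits is such a reason. Scripted telephone screening may even ensure that it is asked. This stands. What remains is classification: the reason would sit among exclusions rather than refusals.
- **No rate is shown to be biased.** A reader might infer that the exclusion inflates the recruitment rate on which a randomised trial would be planned. The documents do not support this. The criterion is a count. The Abstract mentions recruitment rates, but no denominator is defined, and uptake among eligible people is nowhere named as a planning figure.
- **Recruitment has reserves.** The protocol provides further routes, and larger and more frequent mailings if numbers fall short. This lowers the risk of missing 15 in a year. It is not a reason to turn away people whom the design can already accommodate.
- **The screening script is not shown.** Callers may hear about the other location before they answer. That is possible, but the written criterion still excludes on discomfort with home visits alone.

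**Conclusion.** The contradiction holds, because it lies in what the article states and not in what it leaves out. As written, the exclusion removes people who would take part at the alternative location. It narrows the pool for the 15-in-1-year criterion without need, and it sits poorly with the aim of broad recruitment. It also classes home-visit discomfort as ineligibility.

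The size is unknown. The loss of recruits depends on how many people are uncomfortable with home visits and how many of them would accept another place, and the documents give neither. No threshold or analysis rests on this line, so the consequence is limited to recruitment and to how non-participation is read.

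**What to change.** Reconcile the Participants text and Table 1 with the recruitment, Intervention and Discussion sections:

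1. Limit the exclusion, in both places, to people unwilling to have in-person sessions either at home or at a mutually agreed private location.
2. Record discomfort with home visits as its own reason at screening, whatever the person then decides, and record the location used by those who enrol.
3. If a recruitment rate is reported, show people lost for this reason on a separate line, including those who refuse both locations. The latter remain excluded under the new wording, so the rate should be readable with and without them.

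The cost is a minor eligibility amendment and one code in the screening log. No extra resources are needed, since the alternative location is already part of the design.

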### Intervention

The hybrid RT program will include a combination of in-person and virtual delivery of live exercise sessions (Table 2). The intervention will be delivered by study staff specifically trained in the delivery of exercise programs for individuals with cancer. The first 2 weeks will include a member of the study team visiting the home of participants (or other mutually agreed upon private location) two times per week to deliver supervised exercise sessions. The purpose of this phase is to (1) determine a safe place to exercise in the individual’s home or mutually agreed upon, private location and (2) provide in-person instruction on safe exercise technique and general procedure for exercise sessions (sets, repetitions, clusters, anchoring of perceived exertion/dyspnea scales, etc.). Selection of exercises and loading will be based on each individual’s strength levels, mobility, and any physical limitations. Participants will be provided dumbbells, kettlebells, and suspension training bands (TRX, San Francisco, USA) to complete the home-based exercises. In addition to exercise selection and the delivery of exercise sessions as above, the initial 2 weeks of the study period will also be used to guide participants on how to use the computer tablets, log in for exercise sessions, and record their exercise participation/RDI. Moreover, written instructions in plain language will be provided. Tablet stands will also be provided to allow for more flexibility regarding the placement of tablets for easy viewing.

**Table 2 Tab2:** Overview of hybrid delivery approach for the program

	Weeks																					
	1		2		3			4			5			6			7			8		
Video					X	X	X	X	X		X	X	X	X	X		X	X	X	X	X	
In person	X	X	X	X						X						X						X

The exercise sessions will include a warm-up, “main session” including six total movements targeting total body musculature (hip hinge, squat, horizontal push, vertical push, horizontal pull, trunk), and a cool-down period. The exercise program is designed acknowledging some of the limitations of home-based exercise and equipment availability. Moreover, the protocol will initially be piloted on 2–3 individuals prior to the trial. Specifically, the study staff will identify several individuals who are representative of the target study population. These individuals will undergo the same eligibility screening as program participants. If deemed eligible, participants will be asked to come to the laboratory at the University of South Carolina to pilot the program, in line with procedures from a recently published study on designing home-based exercise programs among older adults [17]. Individuals will take part in the exercise program on two separate occasions. Individuals will then be asked to provide experience on all aspects of the program (level of technicality, perceived level of difficulty, safety concerns, and potential challenges). This feedback will be used to finalize the exercise protocol for the trial. The final exercise protocol will be presented in its entirety in future publications.

Sessions will be progressed by adding sets/repetitions to the exercises and increasing load as appropriate and tolerated (i.e., in exercises where no load can be added, a focus will be on adding sets or changing body position to adjust moment arm lengths). Specifically, trained staff on the trial will select the appropriate exercises, provide coaching cues for safe movement, and tailor exercise sessions for each individual. To assist with transparency and reproducibility, de-identified training logs including exercise selection, sets, repetitions, and load will be made available on an open access repository after completion of the study, in line with other exercise oncology studies [21]. Following the 2-week in-person period, participants will be asked to complete 3 sessions per week using live, virtual sessions. These sessions will be delivered in a ratio of up to 4:1 of participants to instructor. Every sixth session, the exercise session will be delivered in-person to address any concerns, provide modifications if necessary, and ensure safe progression of exercises. Individuals will be given the option of a paper- or tablet-based (using tablets provided) program to record aspects of intervention fidelity (sets, repetitions, and weight), dyspnea with exercise, and perception of effort. Reasons for missing sessions will be recorded. Missed sessions will not be made-up through extra sessions during the 8-week training period.

### Study outcomes

Study outcomes will be assessed within 1 week of initiation and at program completion. The exit interview will be conducted within 2 weeks of program completion. An overview of assessments is provided in Table 3.

**Table 3 Tab3:** Overview of testing and timeline of study activities

Outcomes	Baseline	Weeks 1–8	Post-testing
Informed consent, medical history, and demographics	X		
Feasibility outcomes: recruitment, retention, fidelity, acceptability	X	X	X
Health/wellness questionnaires: dyspnea, fatigue, quality of life	X		X
Body composition: dual-energy X-ray absorptiometry (DEXA)	X		X
Muscular strength: 5 repetition maximum	X		X
Physical function: 6-min walk test and 5 timed sit to stand	X		X
Exit interview			X

### Outcome measures

The primary outcome of feasibility will be evaluated by (1) recruitment (successful recruitment of target sample size, *n* = 15, in 1 year); (2) retention (number of participants who complete follow-up assessments, with a threshold set at ≥75%); (3) intervention fidelity (proportion of exercise completed, relative to what was prescribed, with ≥70% considered successful) [19]; and (4) intervention fidelity: if relative dose intensity (RDI) (outlined above) is ≥70%.

#### Acceptability

Intervention acceptability will be assessed using a 10-item questionnaire adapted from McDonnell et al., assessing the acceptability of intervention components on a 4-point Likert-type scale from “Strongly disagree” to “Strongly agree” [22]. Specifically, individuals will be asked about the ease of use of the tablet, utility of virtual exercise sessions, and level of personalization of the program. Additionally, individuals will be asked to participate in an exit interview at the end of the study to learn about their experiences and opinion of the program. Focus groups will be inductive in nature and allow participants to elaborate on their experiences and perceptions of the program. Interviews will be recorded, transcribed, and coded for thematic analysis (nVivo Software, QSR International, Burlington, MA, USA).

#### Dyspnea

Dyspnea will be assessed using the FACIT-Dyspnea (FACIT-D) 10-Item short form [23]. The FACIT-D is divided into two, 10-item scales that assess the level of dyspnea experienced with different activities (part 1) and the difficulty performing various activities as a result of dyspnea in the preceding 7 days (part 2). The scale is scored on a Likert-type response from “no shortness of breath” to “severely short of breath” (part 1) or “no difficulty” to “much difficulty” (part 2).

#### Fatigue

The FACIT-Fatigue scale is a 13-item scale that will be used to assess cancer-related fatigue [24]. The FACIT-Fatigue scale is scored on a 0–4 response scale from 0 = “not at all” to 4= “very much,” regarding items related to fatigue and energy in the past 7 days.

#### Quality of life

Quality of life will be assessed using the Functional Assessment of Cancer Therapy-Lung Cancer Subscale (LCS) [25]. The LCS is a 9-item scale assessing multidimensional aspects of quality of life relating to lung cancer. Items are scored on a 5-point Likert scale from 0 = “not at all” to 4 = “very much,” anchored to the past 7 days.

#### Five-repetition maximum

Muscular strength will be assessed using five-repetition maximum (5RM) testing for leg press and chest press exercises. These are standard tests commonly used in exercise oncology trials [19, 26, 27]. Participants will be asked to perform a general warm-up, followed by two exercise-specific warm-up sets (4–6 repetitions) with increasing load, separated by 90–180s of rest. Participants will then be asked to complete a 5RM attempt (the amount of weight an individual can lift with proper technique through a full range of motion). A 5RM score will be determined when the participant can no longer complete 5 full, safe repetitions of each exercise. In this case, the last load completed safely will be recorded as the 5RM [19, 26, 27]. Approximately 3 min of rest will be provided between attempts and efforts will be made to ensure a 5RM is reached in as few attempts as possible.

